## Abstract

**Background:**

Oral appliance therapy (OAT) is a widely used treatment for obstructive sleep apnea; however, titration approaches remain variable and lack standardization across clinical practice. Existing evidence is largely derived from academic or specialty sleep centers, with limited data on how titration strategies are implemented and perform in real-world dental settings.

**Objective:**

This study aims to evaluate real-world titration approaches for OAT within a dental practice-based research network and to assess their impact on treatment effectiveness and patient-centered outcomes.

**Methods:**

This prospective, multisite, observational feasibility study will enroll approximately 60 adult patients with physician-diagnosed obstructive sleep apnea receiving OAT from 10 dental practitioners within the South Texas Oral Health Network, with each practitioner enrolling up to 6 patients. Practitioners will apply either standard signs-and-symptoms–based titration or enhanced multimethod positioning titration, as per their usual clinical practice. Clinical, dental, and titration characteristics will be collected at baseline and follow-up visits over an approximately 8-week titration period. The primary outcome is mean disease alleviation, calculated as the product of physiologic efficacy (change in apnea–hypopnea index derived from multinight home sleep apnea testing) and objective adherence (hours of nightly oral appliance use captured via an embedded compliance tracker). Secondary outcomes include daytime sleepiness, sleep-related quality of life, patient satisfaction, oral appliance–related side effects, and bruxism. Descriptive analyses and generalized estimating equation models will be used to account for clustering of patients within practitioners.

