## Methods

### Study Design and Setting

This is a prospective, multisite, observational feasibility study to evaluate real-world titration strategies for OAT in OSA. The study examines two titration approaches defined by the American Academy of Dental Sleep Medicine (AADSM) (Figure 1): (1) standard signs-and-symptoms–based titration and (2) enhanced multimethod positioning, which incorporates objective physiologic measures such as pulse oximetry or HSAT. Both approaches are implemented as part of routine clinical care. This study is a nonrandomized, observational investigation designed to evaluate differences in treatment effectiveness between standard signs-and-symptoms–based titration and enhanced multimethod positioning approaches. A clustered design is used, with patients nested within dentists, reflecting real-world clinical practice. Participating dentists who use both titration approaches will apply their usual method for the first 3 enrolled patients and will subsequently be asked to use the alternate approach for the remaining patients, allowing for within-practitioner comparisons. Dentists who routinely use only one titration method will continue to apply that approach consistently across all enrolled patients. For each patient, the selected titration approach is maintained throughout the titration period.

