**Figure 1. F1:**
[figure not shown]
American Academy of Dental Sleep Medicine (AADSM) recommended framework for methods for positioning oral appliance. HRPO: high resolution pulse oximetry; HSAT: home sleep apnea test; PO: pulse oximetry; PSG: polysomnogram.

A total of 60 patients (approximately 6 per dentist) will be enrolled across 10 participating dentists over a 24-month study period, with a planned allocation favoring the enhanced titration approach to support feasibility assessment. Oral appliance therapy is delivered using MADs within routine care, with clinicians retaining discretion over device selection and design features. No protocol-driven training or mandated switching between approaches is imposed, and clinicians continue to follow their usual clinical practices. While this design enhances ecological validity, it may introduce variability related to practitioner and patient factors. These will be addressed analytically through adjustment for measured confounders and the use of generalized estimating equation models to account for clustering of patients within dentists. As a feasibility study, the primary focus is on recruitment, retention, data completeness, protocol adherence, and estimation of preliminary effect sizes to inform future interventional trials. This study protocol is reported using a structured format aligned with STROBE (Strengthening the Reporting of Observational Studies in Epidemiology) guidelines for observational studies [26].

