The study is conducted within the STOHN, a regional dental practice–based research network comprising approximately 379 members across private practices, community-based clinics (eg, Federally Qualified Health Centers), and academic or faculty practice settings. Eligible practitioners must meet the following criteria: (1) be a licensed dentist (general dentist or specialist) and a current member of STOHN; (2) be qualified in dental sleep medicine (DSM), as demonstrated through prior training, continuing education, or clinical experience in managing patients with OSA; (3) have treated at least 3 patients with physician-diagnosed OSA using OAT within the past 12 months; (4) complete required human subjects protection training and study-specific training prior to patient enrollment; (5) agree to apply a defined titration approach consistently to all enrolled patients. Dentists from a range of practice settings are eligible, with no restrictions on practice type. Both general dentists and dental specialists may participate. Exclusion criteria for practitioners include participation of more than one dentist from the same practice site to minimize potential inter-dentist contamination.

Dentists from the Southwest Region of the National Dental -PBRN (n=1678) were invited to participate. In addition, the study’s principal investigators encouraged eligible colleagues within the National Dental PBRN, including those outside the Southwest Region, to participate. Eligibility criteria were consistently applied to all invited practitioners.

The study is coordinated by the University of Texas Health Science Center at San Antonio (UTHSA) Clinical Research Informatics/Data Coordinating Center and supported by Clinical and Translational Science Award infrastructure. Participating practices serve as recruitment and data collection sites. Dentist enrollment has been initiated, and patient enrollment is ongoing at the time of manuscript submission. The anticipated study duration is 24 months.

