#### Sample Size

Sixty patients will be enrolled across 10 dentist clusters (approximately 6 patients per dentist). This sample size was determined to support feasibility objectives and to estimate variability in the primary outcome (MDA) [7,10] while accounting for clustering of patients within dentists. Assuming a 2-sided α of .05 and 80% power, the study is capable of detecting standardized differences in MDA ranging from approximately 0.82 to 0.97, depending on assumptions regarding intracluster correlation coefficients (5%‐10%) and allocation ratios between titration approaches (4:6 or 3:7). These calculations account for an anticipated attrition rate of 10%‐20%.

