## Results

The PAOSA study was funded on June 17, 2025, and received IRB approval from the UTHSA in September 2025. Study start-up activities, including coordination with device vendors (NightOwl and DentiTrac), development of data collection systems, and preparation of training materials. Dentist recruitment and onboarding began in late 2025. Between December 2025 and March 2026, 7 dentists have completed human subjects protection and study implementation training, have been enrolled in the study, and have initiated patient recruitment. All trained dentists were cleared to begin patient recruitment following completion of study readiness activities. An additional 3 dentists are in the process of completing training.

Patient recruitment began in late 2025 during routine clinical care visits. The planned sample size is 60 patients, with approximately 6 patients per dentist. The study aims to enroll 60 patients, with approximately 6 per dentist. Recruitment is projected to continue through January 2027. Data collection includes baseline assessments and follow-up visits at approximately 4 and 8 weeks, along with integration of physiologic and adherence data from device-based systems. Final analyses are planned following completion of recruitment and follow-up, with study completion projected for June 16, 2027.

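### Capping each of 10 dentists at 6 patients makes 60 a maximum, and the stated detectable difference of 0.82 to 0.97 holds only if all 60 are analysed

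*Protocol article*

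**What the plan says.** The enrolment rule appears in four places in the protocol article.

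- Abstract, Methods: the study "will enroll approximately 60 adult patients with physician-diagnosed obstructive sleep apnea" from 10 practitioners, "with each practitioner enrolling up to 6 patients". This is a ceiling per dentist with an approximate total.
- Methods, Study Design and Setting (text after Figure 1): "A total of 60 patients (approximately 6 per dentist) will be enrolled across 10 participating dentists". This is an approximate number per dentist with a definite total.
- Methods, Sample Size: "Sixty patients will be enrolled across 10 dentist clusters (approximately 6 patients per dentist".
- Results: "The planned sample size is 60 patients, with approximately 6 patients per dentist".

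The Sample Size section then gives the precision. "Assuming a 2-sided α of .05 and 80% power", the detectable standardized difference in mean disease alleviation is about 0.82 to 0.97, for intracluster correlations of 5% to 10% and allocation of 4:6 or 3:7. It adds that these calculations allow for attrition of 10% to 20%.

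The only figure for practice volume is the dentist eligibility criterion in the Methods: "have treated at least 3 patients with physician-diagnosed OSA using OAT within the past 12 months".

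**The concern.** A ceiling and an average are different rules. If 6 is an average, a busy practice can make up for a slow one. If 6 is a ceiling, it cannot, and 10 dentists can supply 60 patients only when all of them fill. The article does not say which rule applies, or what happens when a dentist falls short.

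This matters because the printed detectable difference appears to need 60 patients in the analysis. With 60 as the most that can be enrolled, any dropout puts the analysed number below 60, and the cap rules out enrolling more to compensate. A reader who plans the follow-on trial from this article would take the precision of the comparison to be better than the design can give.

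**Working it through.** **Inputs, all from the Sample Size section:** two-sided alpha 0.05; power 80%; 10 clusters; 60 patients enrolled; intracluster correlation (ICC) 0.05 to 0.10; smaller-arm share p = 0.4 or 0.3; attrition 10% to 20%.

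**Formula** (normal approximation, two means, SD = 1, usual design effect):

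d = (1.960 + 0.842) × √[DE / (N·p·(1 − p))], with DE = 1 + (m − 1)·ICC and m = N/10.

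**Step 1. Reproduce the printed range.** Take N = 60 analysed and m = 6.

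- ICC 0.05, 4:6: DE = 1.25; N·p·(1 − p) = 14.4; d = 2.802 × √(1.25/14.4) = 0.825.
- ICC 0.10, 3:7: DE = 1.50; N·p·(1 − p) = 12.6; d = 2.802 × √(1.50/12.6) = 0.967.

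This matches both printed ends, with no attrition.

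**Step 2. Apply the stated attrition to 60 enrolled.** Analysed: 60 × 0.90 = 54, or 60 × 0.80 = 48.

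- Best case, N = 54, m = 5.4, ICC 0.05, 4:6: DE = 1.22; d = 2.802 × √(1.22/12.96) = 0.860.
- Worst case, N = 48, m = 4.8, ICC 0.10, 3:7: DE = 1.38; d = 2.802 × √(1.38/10.08) = 1.037.

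The range is about 0.86 to 1.04. Other conventions do not recover the printed figures: holding m at 6 gives 0.87 to 1.08, and a t instead of a normal reference gives 0.88 to 1.06. Even the most favourable stated inputs give 0.86 once 10% are lost, so the lower end of 0.82 cannot include attrition.

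**Step 3. Power at the printed differences.**

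| Analysed | Power at 0.82 (ICC 0.05, 4:6) | Power at 0.97 (ICC 0.10, 3:7) |
|---|---|---|
| 60 | 79.5% | 80.3% |
| 54 | 76.2% | 77.7% |
| 48 | 72.3% | 74.6% |

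**Step 4. What the cap allows.** The maximum is 10 × 6 = 60. To analyse 60, enrolment would have to be 60/0.90 = 66.7, so 67, or 60/0.80 = 75. Neither is possible with 10 dentists capped at 6.

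**Step 5. How sensitive the total is to practice volume.** The documents give no actual volumes, so this step is illustrative. Let the number of enrollable patients per dentist over the whole window be Poisson with an assumed common mean, capped at 6.

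| Assumed mean per dentist | Expected total | Chance that all 10 fill |
|---|---|---|
| 3 | 29.5 | under 0.1% |
| 6 | 50.4 | 0.3% |
| 8 | 56.5 | 12% |
| 10 | 58.9 | 50% |
| 12 | 59.7 | 81% |

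The expected total runs from about 30 to almost 60. If only 50 were enrolled, 45 to 40 would be analysed after attrition and the range would be 0.92 to 1.10.

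**The case against.** The strongest reply is that the criterion of 3 patients in 12 months is a floor. A reader might infer from it that the study will miss 60: filling 6 takes about 5.1 enrolments a year over an assumed 14 months (6 × 12/14), or 7.2 a year over an assumed 10 months for the 3 dentists still in training. The documents do not support that inference. No dentist's actual volume is given, larger practices can fill 6, and the totals in Step 5 depend on assumed means. The Abstract also promises only approximately 60, so a shortfall of two or three patients would be no failure.

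A second tempting inference is that slow recruitment will destroy the within-dentist comparison, because dentists who use both approaches "will apply their usual method for the first 3 enrolled patients" and change only afterwards. That touches only dual-method dentists near the minimum volume, and their number is not stated.

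A third inference is that the volume criterion should be raised. Seven dentists are enrolled and three are completing training, so all ten appear to be identified and a change would do little.

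It is also fair to say that recruitment and retention are themselves objects of this feasibility study, and that the January 2027 end of recruitment is a projection with completion planned for June 2027. Under-recruitment would be a reportable result.

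These points dispose of any claim that 60 will not be reached. They do not settle ceiling against average, and they do not rescue 0.82 to 0.97: that range fails under the stated attrition even if every dentist fills the quota.

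**Conclusion.** The point holds in two parts.

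- **Enrolment rule.** The article states a ceiling in one place and an average in three. Read as a ceiling, 60 is a maximum with no slack. A shortfall is a risk whose size cannot be judged from the documents. Taken alone, this is a minor clarification.
- **Detectable difference.** The printed 0.82 to 0.97 corresponds to 60 analysed patients, although the text says attrition is covered. With 60 enrolled and 10% to 20% lost, it is about 0.86 to 1.04. This is the firmer part, and it does not depend on practice volume. The cap adds to it by excluding compensating enrolment.

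The figures assume equal cluster sizes, the normal approximation and the simple design effect. That formula reproduces both ends of the printed range at N = 60, so it is probably the one used. The shift is modest, and for a feasibility study it affects how precision is described more than whether the study is worth doing.

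**What to change.** 1. Use one rule in the Abstract, Study Design and Setting, Sample Size and Results: 6 per dentist is a target, the total is fixed at 60, and places left unfilled at one practice may be taken up by dentists who have already enrolled 6. Dentists who use both approaches should keep the two balanced in number when they take extra patients, since simply extending the present order would add only to the second approach.
2. In Sample Size, restate the detectable difference as about 0.86 to 1.04 for 54 to 48 analysed patients.
3. If the ceiling is kept instead, call 60 a maximum.

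The cost is a wording amendment and one restated figure, with no enrolment beyond 60. The downside is modestly unequal clusters. With a cluster-size coefficient of variation of 0.5 (assumed), DE = 1 + [(1 + 0.25)·m − 1]·ICC. At N = 60 before attrition, DE is 1.325 or 1.65 and the range is 0.85 to 1.01. After attrition, DE is 1.2875 (N = 54) or 1.50 (N = 48), so d = 2.802 × √(1.2875/12.96) = 0.88 to 2.802 × √(1.50/10.08) = 1.08. That is slightly better than the 0.92 to 1.10 that would follow from enrolling only 50 in equal clusters.

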**Results:**

The study was funded on June 17, 2025, and received Institutional Review Board approval from the University of Texas Health Science Center at San Antonio as the single reviewing Institutional Review Board (STUDY00001750), with site-specific approval obtained from the University of Illinois Chicago (SITE00000057). Study start-up activities, including development of data systems and coordination with device vendors, were completed between September and December 2025. Practitioner training was conducted between December 2025 and February 2026. As of March 2026, 7 dentists have been enrolled and have initiated patient recruitment. Participant recruitment began in late 2025 and is projected to continue through January 2027. Data analysis is anticipated in 2027, with study findings expected to be disseminated thereafter.

**Conclusions:**

This study will generate preliminary, real-world evidence on oral appliance titration strategies and their relationship to treatment effectiveness and patient outcomes in community dental practices. Findings will inform the design of future interventional trials and support the development of evidence-based guidance for OAT titration.

## Introduction

Obstructive sleep apnea (OSA) is a highly prevalent and underdiagnosed chronic disease characterized by repeated upper airway collapse during sleep, resulting in hypoxemia, sleep fragmentation, and sympathetic nervous system activation. Globally, OSA affects an estimated 9%‐38% of adults. In the United States, OSA is estimated to affect approximately 12% of the adult population, corresponding to nearly 54 million individuals, with up to 80% of cases remaining undiagnosed [1-4]. Untreated OSA is associated with substantial morbidity and mortality, including cardiovascular disease, metabolic dysfunction, neurocognitive impairment, motor vehicle accidents, and diminished work productivity [5]. The economic burden is profound, with undiagnosed OSA alone estimated to cost the US health care system US $149.6 billion annually [1].

Continuous positive airway pressure (CPAP) remains the first-line treatment for OSA; however, long-term adherence is poor, with fewer than half of patients maintaining adequate nightly use [6-8]. As a result, oral appliance therapy (OAT), particularly mandibular advancement devices (MADs), has become an increasingly important alternative, especially for patients with mild to moderate OSA or those intolerant of CPAP [6,8,9]. When patient adherence is considered, OAT produces clinical outcomes comparable to CPAP for many patients [7,10,11].

The therapeutic success of OAT depends on accurate titration, that is, the individualized advancement of the mandible to achieve airway patency while minimizing temporomandibular discomfort and dental side effects. The optimal therapeutic position varies substantially among patients, making titration a critical, highly individualized component of care [12]. The American Academy of Dental Sleep Medicine (AADSM) recognizes two primary approaches to titration: (1) signs-and-symptoms–based titration, relying on patient-reported outcomes such as snoring and sleepiness, and (2) multimethod positioning, which incorporates objective measures such as pulse oximetry and home sleep apnea testing (HSAT) during titration [12]. Despite widespread use of both strategies, no comparative real-world evidence exists to determine which approach optimizes outcomes, and no uniform consensus guides dental sleep medicine practice [12,13].

Traditional measures of OAT effectiveness have focused on reductions in the apnea–hypopnea index (AHI); however, AHI alone does not reflect real-world treatment benefit because adherence to therapy varies substantially across patients. Objective compliance monitoring using embedded micro trackers enables precise quantification of nightly appliance use and calculation of mean disease alleviation (MDA), which integrates both treatment efficacy (AHI reduction) and adherence [7,10]. MDA is now recognized as a superior measure of therapeutic effectiveness for OAT [7,10,14]. Advances in digital health technologies now enable the integration of objective physiologic and adherence data in routine clinical practice. The DentiTrac tracker provides objective adherence data [15], while multinight HSAT, for example, NightOwl, provides physiologic measures of sleep-disordered breathing as an alternative to polysomnography in appropriately selected patients [16-18]. Together, these tools allow for more precise and scalable evaluation of treatment effectiveness in real-world settings.

Most studies evaluating OAT titration have been conducted in academic or specialty sleep centers, limiting their generalizability to real-world dental practice. Practice-based research networks (PBRNs) offer a validated infrastructure for studying care delivery in real-world clinical environments [19-21]. The South Texas Oral Health Network (STOHN) PBRN [22,23], in collaboration with the National Dental Practice-Based Research Network (PBRN) [19-21,24], serves a highly diverse patient population, including large Hispanic, publicly insured, and uninsured communities, providing a uniquely representative setting for evaluating OSA care. Dental PBRNs facilitate the study of clinically relevant questions by integrating research into routine practice. A 2021 National Dental PBRN survey of 311 dental practitioners (general dentists and specialists) found that titration, patient compliance, and management of side effects were among the most important and least understood aspects of dental sleep medicine practice [25]. These findings highlight a critical need for practice-based, objective evidence to guide OAT titration.

The primary objective is to evaluate the feasibility and preliminary comparative effectiveness of two oral appliance therapy (OAT) titration approaches, standard signs-and-symptoms–based titration and enhanced multimethod positioning as implemented in routine clinical practice.

## Methods

### Study Design and Setting

This is a prospective, multisite, observational feasibility study to evaluate real-world titration strategies for OAT in OSA. The study examines two titration approaches defined by the American Academy of Dental Sleep Medicine (AADSM) (Figure 1): (1) standard signs-and-symptoms–based titration and (2) enhanced multimethod positioning, which incorporates objective physiologic measures such as pulse oximetry or HSAT. Both approaches are implemented as part of routine clinical care. This study is a nonrandomized, observational investigation designed to evaluate differences in treatment effectiveness between standard signs-and-symptoms–based titration and enhanced multimethod positioning approaches. A clustered design is used, with patients nested within dentists, reflecting real-world clinical practice. Participating dentists who use both titration approaches will apply their usual method for the first 3 enrolled patients and will subsequently be asked to use the alternate approach for the remaining patients, allowing for within-practitioner comparisons. Dentists who routinely use only one titration method will continue to apply that approach consistently across all enrolled patients. For each patient, the selected titration approach is maintained throughout the titration period.

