### Study Population

The study population comprises adult patients receiving OAT for OSA in participating dental practices within the STOHN. Eligible participants must meet the following criteria: (1) be aged 18 years or older; (2) have a confirmed diagnosis of OSA established by a qualified sleep physician; (3) have a referral for OAT with a scheduled oral appliance delivery visit at a participating site; (4) be able to communicate in English; (5) have access to email or text messaging for study communication; (6) be willing to complete HSAT using the NightOwl device [16,17]; (7) agree to use an oral appliance embedded with an objective compliance tracker (DentiTrac) [15].

Participants will be excluded if they: (1) lack a physician-confirmed diagnosis of OSA;

(2) have a history of OSA-related surgical treatment (eg, tonsillectomy and/or adenoidectomy or uvulopalatopharyngoplasty [UPPP]); (3) are unable to provide reliable contact information; and (4) decline participation in device-based monitoring. Participants are recruited consecutively from eligible patients receiving routine clinical care at participating sites. The titration approach is determined by the treating practitioner and applied consistently to enrolled patients within each practice.

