Strengths of this study include its PBRN design, integration of objective physiologic and adherence data, and evaluation of titration strategies within routine clinical workflows. The PBRN design is a major strength of this study. PBRNs provide a validated infrastructure for evaluating clinical care in real-world settings across diverse populations and practice models [19-21]. Conducted within the STOHN and in collaboration with the National Dental PBRN, PAOSA reflects the heterogeneity of real-world dental practice and enhances the external validity and applicability of study findings [25].

Several limitations should be considered. The observational, nonrandomized design introduces the potential for residual confounding and selection bias, although the structured within-practitioner approach was implemented to reduce between-practitioner variability. The relatively short follow-up period focuses on early treatment response and may not capture long-term adherence patterns or dental changes. In addition, eligibility requirements related to language and device use may limit participation among some populations. These limitations are appropriate for a feasibility-focused study and are expected to inform the design of subsequent interventional trials. As a feasibility protocol, PAOSA is designed to generate critical data on recruitment, retention, data completeness, protocol adherence, and preliminary effect-size estimates to support future randomized or pragmatic trials. The study will also identify practical barriers and facilitators to integrating HSAT and objective adherence monitoring into routine dental workflows, both of which are essential for scalability and sustainability.

Future directions include the development of randomized or hybrid effectiveness-implementation trials to more definitively evaluate titration strategies, as well as expansion to broader populations and longer follow-up periods. Study findings will be disseminated through peer-reviewed publications, presentations at scientific meetings, and communication within the dental practice–based research network to support translation into clinical practice.

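### The rule assigning titration approach contradicts itself: some dentists are asked to switch after 3 patients, yet all must keep one approach for every patient

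*Protocol article*

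**What the plan says.** Two descriptions of how approach is assigned stand in the same article.

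**Switching.** Study Design and Setting has an instruction for dentists who use both approaches: "apply their usual method for the first 3 enrolled patients and will subsequently be asked to use the alternate approach". Their later patients thus receive the other method, and the article gives the purpose of this as "allowing for within-practitioner comparisons". Dentists with a single method keep it throughout. The limitations paragraph of the Discussion concedes possible residual confounding and selection bias, "although the structured within-practitioner approach was implemented to reduce between-practitioner variability".

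**No switching.**
- Practitioner eligibility criterion 5, in the same Methods section: each dentist must "agree to apply a defined titration approach consistently to all enrolled patients".
- Study Population: "The titration approach is determined by the treating practitioner and applied consistently to enrolled patients within each practice".
- The paragraph after Figure 1: "No protocol-driven training or mandated switching between approaches is imposed, and clinicians continue to follow their usual clinical practices".

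Sample Size assumes 60 patients, 10 dentists, an intracluster correlation (ICC) of 5% to 10% and "allocation ratios between titration approaches (4:6 or 3:7"). It gives detectable differences of about 0.82 to 0.97 SD. The analysis paragraph names a two-level approach term, clustering by dentist and confounder adjustment.

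**The concern.** Approach is the exposure. The assignment rule decides whether the comparison runs within dentists, between dentists or both. It also decides the allocation ratio, the detectable difference and what counts as a protocol deviation. Protocol adherence is one of the study's stated feasibility aims, yet under the present text a switch is compliance by one passage and a breach by another.

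The Discussion's claim of reduced between-practitioner variability holds only if some dentists do switch. Where they do, the usual method always comes first, so approach and enrolment order cannot be told apart inside that dentist. Seven dentists had begun recruiting by March 2026 and three more were in training, so the rule in force already matters.

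**Working it through.** **1. Can the passages be reconciled?** The request to switch covers only dentists who use both approaches. Criterion 5 and Study Population cover all enrolled patients with no carve-out. Only one dentist per practice may take part, so constancy within a practice means constancy within a dentist. The sentence about keeping the approach through the titration period concerns a single patient and does not help. The conflict with the paragraph after Figure 1 is softer, because being asked is not being mandated. Even so, using the alternate method on request is not simply continuing usual practice.

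**2. The plan's own figure.** Detectable difference = (1.960 + 0.842) × √[(1 + 5 × ICC)(1/n₁ + 1/n₂)], with 6 patients per dentist and all 60 analysed.

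| ICC | 24 vs 36 (4:6) | 18 vs 42 (3:7) |
|---|---|---|
| 0.05 | 0.825 | 0.882 |
| 0.10 | 0.904 | 0.967 |

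The stated range is reproduced. The full design effect, 1 + 5 × ICC, applies when every dentist uses one approach (4 vs 6 or 3 vs 7 dentists), so the calculation is for the no-switching version.

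**3. Allocation.** A switcher with 6 patients puts 3 in each arm, so s switchers put at least 3s in the smaller arm. A 3:7 split needs 3s ≤ 18, so s ≤ 6. A 4:6 split needs 3s ≤ 24, so s ≤ 8. If all 10 switch, the split is 30:30.

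**4. Pooled model with switchers.** Under exchangeable correlation the pooled estimate combines two sources of information:
- within dentists: precision s / [(1 − ICC)(1/3 + 1/3)];
- between dentists: precision Sxx / [(1 + 5 × ICC)/6], where Sxx is the sum of squares, about its mean, of each dentist's share of patients on enhanced.

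Worked case (assumed mix): 4 same-order switchers, 2 standard-only and 4 enhanced-only dentists, ICC 0.10.
- Within: 4/0.6 = 6.667.
- Between: mean share 0.6; Sxx = 2(0.36) + 4(0.01) + 4(0.16) = 1.40; 1.40/0.25 = 5.6.
- Detectable difference: 2.802/√12.267 = 0.800.

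**5. Order effect.** Patients 4–6 follow patients 1–3 by 3 places on average. An assumed trend of 0.1 SD per successive patient shifts the contrast in one switching dentist by 0.30 SD. With same-order switchers, pooled bias = 0.30 × within precision / total precision. In the worked case this is 0.30 × 6.667/12.267 = 0.163.

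**6. Adding a first-3/last-3 period term.** With same-order switchers the within precision falls to s(10 − s)/10 ÷ 0.6 at ICC 0.10. In the worked case this is 2.4/0.6 = 4.0, and the detectable difference becomes 2.802/√9.6 = 0.904.

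Results at ICC 0.10 (all dentist mixes are assumptions):

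| Switchers; standard-only; enhanced-only | Detectable | Pooled bias | Detectable with period term |
|---|---|---|---|
| 3 same order; 2; 5 | 0.841 | 0.135 | 0.904 |
| 4 same order; 2; 4 | 0.800 | 0.163 | 0.904 |
| 4 split 2/2 by usual method; 2; 4 | 0.800 | 0 | 0.800 |
| 6 same order; 1; 3 | 0.760 | 0.221 | 1.016 |
| 10 same order | 0.686 | 0.300 | not estimable |
| 10 split 5/5 by usual method | 0.686 | 0 | 0.686 |

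At ICC 0.05 the 3-switcher mix gives 0.118, the lower end of the 0.12 to 0.22 range. Bias is proportional to the trend: 0.05 SD per patient turns that range into 0.06 to 0.11, and 0.2 SD into 0.24 to 0.44.

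**The case against.** The strongest defence has four parts.

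- **The request is soft and limited.** It goes only to dentists who already use both methods, and training and workflow binders, which are not shown, may give sites one clear rule. This softens the conflict with the paragraph after Figure 1. It also means the documents do not show that sites are following different rules, though a reader might infer that. It does not reconcile criterion 5 or Study Population.
- **The order effect is not general.** A reader might conclude that the comparison is fully confounded with time. That is true of usual versus alternate inside a switching dentist. The study compares standard with enhanced, and the usual method may differ between dentists. Single-method dentists also have early and late patients on the same approach. Complete aliasing needs all 10 to switch in the same order. Dentists must be qualified in dental sleep medicine with recent cases, and switchers already know both methods, which argues against a steep learning trend. This part stands.
- **Switching does not by itself weaken the study.** Taking the within-dentist contrast alone gives detectable differences of 1.25 SD with 3 switchers and 0.97 with 5 (2.802 × √(0.6/s)). That discards between-dentist information which the planned pooled analysis uses. In the mixes tried, switching improves pooled precision. This stands too; what remains is that the sample-size basis describes a different design.
- **This is a feasibility study that admits residual confounding.** True, but the same sentence offers the within-practitioner structure as mitigation, and other passages rule that structure out.

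A reader might also want the coordinating center to balance which approach comes first. That would turn clinician-chosen care into assigned care in a study described as nonrandomized and observational, so it is a debatable trade-off and is not asked for here.

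**Conclusion.** The assignment rule is wrong as written. The request to switch cannot stand beside criterion 5 and the Study Population statement, and the Discussion relies on the version those passages exclude. This rests on the text alone.

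The stated 0.82 to 0.97 SD belongs to the no-switching version. With switchers the allocation moves toward 1:1, and 3:7 is out of reach beyond 6 of them. This assumes 6 patients per dentist and all 60 analysed.

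The order effect is real within each switching dentist, but its effect on the pooled comparison is conditional. At the assumed 0.1 SD per patient it runs from zero (usual methods balanced among switchers) through 0.12 to 0.22 SD (the mixes of 3 to 6 same-order switchers tried) to 0.30 SD (all 10 in the same order). The number of switchers and their usual methods are not given, so no single value can be attached to this study.

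**What to change.** Reconcile Study Design and Setting (including the paragraph after Figure 1 and practitioner criterion 5), Study Population and the Discussion limitations into one assignment rule, and tell the sites already recruiting. The choice between the two versions is the sponsor's.

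**If switching stays:**
- limit the one-approach-for-all wording in criterion 5 and Study Population to single-method dentists, and reword the no-mandated-switching sentence;
- state the sample-size basis for the mixed design, including the expected number of switchers;
- record each switcher's usual method and every patient's enrolment order;
- report the within-dentist contrast, plus a sensitivity analysis with an enrolment-period term where it can be estimated.

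**If switching goes:** delete the within-practitioner statements in Study Design and Setting and in the Discussion. The sample-size basis then already matches the design on this point.

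**Cost:** a wording amendment, which the article says needs IRB approval before it is implemented, a notice to sites and, if switching stays, two recorded items. The period-adjusted analysis is less precise: for example, the detectable difference rises from 0.80 to 0.90 SD with 4 same-order switchers at ICC 0.10. It cannot be fitted at all if every dentist switches in the same order.
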